### **9.5.2 Concomitant medication**

Concomitant medication will be coded using the World Health Organization (WHO) drug dictionary (Version March 2019). Concomitant medication will be listed.

### **9.5.3 Clinical laboratory parameters**

All clinical chemistry and hematology data will be summarized by parameter and treatment, together with changes from baseline, where baseline is defined as the scheduled assessment immediately prior to dosing, and listed. Urinalysis data will be listed. Additionally, clinical chemistry, hematology and urinalysis data outside the reference ranges will be listed.

Values for any clinical chemistry, liver panel, hematology and urinalysis values outside the reference ranges will be flagged on the individual subject data listings.

### **9.5.4 Vital signs**

Automated office blood pressure monitoring data (AOBPM) (systolic blood pressure, diastolic blood pressure and pulse rate) will be recorded. Four records are recorded, the first is discarded and for the latter 3 records, the mean will be calculated and used for reporting and analysing.

Vital signs data and AOBPM data will be summarized by treatment and timepoint together with changes from baseline, where baseline is defined as the Day 1 predose assessment. Figures of

mean vital signs and mean changes from baseline profiles over time will be presented by treatment.

Values for individual subjects will be listed.

The relationship between time-matched systolic blood pressure, diastolic blood pressure, and heart rate from AOBPM data and the LY3475766 PK concentration will be evaluated graphically using a scatter plot. The plot will include a longitudinal linear model with independent variables, PK concentration as a continuous variable and time relative to the first dose time as a categorical variable. A compound-symmetry variance-covariance structure will be used to model the within-subject correlation. If the model fails to converge, an alternative structure will be investigated instead. The estimated regression line and associated 90% CI will be fitted on the plot and the p-value for the slope reported.

Example of SAS code as follows.

```
proc mixed data=xxx;  
class time subject;  
model vital = pk_conc time /residual ddfm=kr;  
repeated time / subject=subject type=cs alpha=0.1;  
run;
```

For the AOPBM data, a repeated-measures statistical analysis of absolute and change from baseline vital sign measurements will be produced with fixed effects for treatment, timepoint, and the interaction treatment and timepoint and baseline as a covariate (for the change from baseline analysis). An unstructured covariance structure will be used and a compound symmetric structure can be used if the model fails to converge. The primary contrasts of interest are each dose level versus placebo at each timepoint. Least squares means as well as a 90% CI of the mean difference between each dose level and placebo will be obtained.

Example of SAS code as follows.

```
proc mixed data=xxx;  
class treatment;  
model change = baseline treatment timepoint treatment*timepoint  
/residual ddfm=kr;  
repeated timepoint / subject=subject type=UN;  
lsmeans treatment*timepoint / cl pdiff alpha=0.1;  
ods output lsmeans=lsm diffs=estims;  
run;
```

For the AOPBM data, for each subject, the maximum value within the 3 and 9 weeks after the first dose will be summarized by treatment, and listed.

In addition, the calculated maximums values will be compared between dose groups using a linear model with treatment as a fixed effect and baseline value as a covariate. The analysis will compare each dose of LY3475766 against placebo. Least-squares means as well as 90% CIs for the difference of LY3475766 compared with placebo will be reported.

Example of SAS code as follows.

```
proc mixed data=xxx;  
class treatment;  
model max = baseline treatment /residual ddfm=kr;  
lsmeans treatment / cl pdiff alpha=0.1;  
ods output lsmeans=lsm diffs=estims;  
run;
```

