| Single-lead telemetry     |                   | X  | X                | X | X | X | X | X | X | X |        |        |        |        |        |           |    | Day 5 through 8 are SC only. Telemetry is continuous from 12 h predose to 72 h postdose (IV cohorts) or 168 h postdose (SC cohorts). |
| Seated PR                 | X                 | X  | X                | X | X | X | X | X | X | X | X      | X      | X      | X      | X      | X         | X  | Day 1: Within 1 h before dosing and 5 to 15 min, 1 h (+ 30 min), and 8 h after starting dosing; Days 5-7 for SC cohorts only         |
| Body temperature          | X                 | X  | P                | X | X | X |   |   |   | X | X      | X      | X      |        |        | X         | X  | Any time before breakfast                                                                                                            |
| Seated BP                 | X                 | X  | X                |   |   |   |   |   |   |   |        | X      |        | X      |        | X         | X  | Day 1: 5 to 15 min and 1 h (+ 30 min) after starting dosing                                                                          |
| AOBPM                     |                   |    | P, 6 h           | X | X | X | X | X | X | X | X      |        | X      |        | X      |           |    | Days 5 through 7 are SC only. See Section 9.4.2. for more details.                                                                   |
| Adverse event reporting   | X                 | X  | ←-----→          |   |   |   |   |   |   |   |        |        |        |        |        | X         |    |                                                                                                                                      |

| Procedure               | Screening         |    | Treatment Period |   |   |   |   |   |   |        |        |        |        |        |        | Follow-up | ET | Notes |
|-------------------------|-------------------|----|------------------|---|---|---|---|---|---|--------|--------|--------|--------|--------|--------|-----------|----|-------|
|                         |                   |    | Week 1           |   |   |   |   |   |   | Week 2 | Week 3 | Week 4 | Week 5 | Week 7 | Week 9 | Week 13   |    |       |
| Day                     | Day -28 to Day -2 | -1 | 1                | 2 | 3 | 4 | 5 | 6 | 7 | 8      | 15 ±2  | 22 ±2  | 29 ±2  | 43 ±5  | 57 ±5  | 85 ±5     |    |       |

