#### **10.3.1.2. Statistical Evaluation of Safety**

Safety parameters that will be assessed include safety laboratory parameters, vital signs, and ECG parameters. The parameters will be listed and summarized using standard descriptive statistics.

The relationship between systolic BP, diastolic BP, and heart rate from AOBPM and the PK concentration will be evaluated through a longitudinal linear model with independent variables of PK concentration as a continuous variable and time relative to the first dose time as a categorical variable. A compound-symmetry variance-covariance structure will be used to model the within-subject correlation.

The mean systolic BP, diastolic BP, and heart rate by dose will be plotted against time. The maximum value (for each subject) within the 9 weeks after the first dose will be summarized and compared between dose groups using a linear model with dose as a factor and baseline mean value of the corresponding analysis variable as a covariate.

Additional analysis will be performed if warranted upon review of the data.

Baseline for safety parameters will be defined as the last evaluable value before the first dose.

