### **3. INTRODUCTION**

This SAP has been developed after review of the Clinical Study Protocol (final version dated 27 June 2019), amendment (a) (final version dated 19 September 2019), amendment (b) (final version dated 12 December 2019), amendment (c) (final version dated 14 February 2020), amendment (d) (final version dated 27 August 2020), final SAP version 1 (dated 25 September 2019), and SAP version 2 (dated 04 September 2020).

This SAP describes the planned analysis of the safety, tolerability, pharmacokinetic (PK) and pharmacodynamic (PD) data from this study. A detailed description of the planned TFLs to be presented in the clinical study report (CSR) is provided in the accompanying TFL shell document.

The intent of this document is to provide guidance for the statistical, PK and PD analyses of data. In general, the analyses are based on information from the protocol, unless they have been modified with Eli Lilly and Company. A limited amount of information concerning this study (e.g., objectives, study design) is given to help the reader's interpretation. This SAP must be signed off prior to first subject treatment administration for this study. When the SAP and TFL shells are agreed upon and finalized, they will serve as the template for this study's CSR.

This SAP supersedes the statistical considerations identified in the protocol; where considerations are substantially different, they will be so identified. If additional analyses are required to supplement the planned analyses described in this SAP, they may be performed and will be identified in the CSR. Any substantial deviations from this SAP will be agreed upon with Eli Lilly and Company and identified in the CSR. Any minor deviations from the TFLs may not be documented in the CSR.

This SAP is written with consideration of the recommendations outlined in the International Conference on Harmonisation (ICH) E9 Guideline entitled Guidance for Industry: Statistical Principles for Clinical Trials and the ICH E3 Guideline entitled Guidance for Industry: Structure and Content of Clinical Study Reports.

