## 9. STATISTICAL METHODOLOGY

### 9.1 General

Data listings will be provided for all data that is databased. Summary statistics and statistical analysis will only be presented for data where detailed in this SAP. For continuous data, summary statistics will include the arithmetic mean, arithmetic standard deviation (SD), median, min, max and N; for log-normal data (e.g. the PK parameters: Area under the concentration

versus time curve [AUCs] and maximum observed drug concentration [ $C_{max}$ ]) the geometric mean and geometric coefficient of variation (CV%) will also be presented. For categorical data, frequency count and percentages will be presented. Data listings will be provided for all subjects up to the point of withdrawal, with any subjects excluded from the relevant population highlighted. Summary statistics and statistical analyses will generally only be performed for subjects included in the relevant analysis population. For the calculation of summary statistics and statistical analysis, unrounded data will be used.

Mean change from baseline is the mean of all individual subjects' change from baseline values. Each individual change from baseline will be calculated by subtracting the individual subject's baseline value from the value at the timepoint. The individual subject's change from baseline values will be used to calculate the mean change from baseline using a SAS procedure such as Proc Univariate.

Data analysis will be performed using SAS® Version 9.4 or greater.

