## **11. CHANGES FROM THE PROTOCOL SPECIFIED STATISTICAL ANALYSES**

There were no changes from the protocol specified statistical analyses.

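### SAP 9.5.4 sets the vital-sign baseline at Day 1 predose, but no seated blood pressure is scheduled then, so its descriptive change from baseline has no baseline as written

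*Combined protocol and SAP*

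**What the plan says.** SAP 9.5.4 treats vital signs and AOBPM as two datasets and plans the same summaries for each: "Vital signs data and AOBPM data will be summarized by treatment and timepoint together with changes from baseline". A single rule then serves both datasets, in these terms: "where baseline is defined as the Day 1 predose assessment". It gives no fallback. SAP 9.1 fixes the calculation: "Each individual change from baseline will be calculated by subtracting the individual subject's baseline value from the value at the timepoint".

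In the Schedule of Activities (protocol Section 2), the note to the seated BP row reads "Day 1: 5 to 15 min and 1 h (+ 30 min) after starting dosing". The note to the seated pulse rate row begins "Day 1: Within 1 h before dosing and 5 to 15 min".

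Protocol 10.3.1.2 has a different rule: "Baseline for safety parameters will be defined as the last evaluable value before the first dose". On precedence, SAP Section 3 states: "This SAP supersedes the statistical considerations identified in the protocol". SAP Section 11 states: "There were no changes from the protocol specified statistical analyses".

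**The concern.** The SAP names a reading that the schedule does not collect for seated BP. A programmer who follows SAP 9.5.4 and 9.1 to the letter has nothing to subtract.

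Clinically significant changes in vital signs are among the primary endpoints, and AOBPM does not cover the same times. Its first post-dose reading is at 6 hours. Seated BP is therefore the only BP scheduled 5 to 15 minutes and 1 hour after dosing starts. In the intravenous cohorts, where protocol 7.1 has infusions of at least 30 or 60 minutes, the earlier of these falls during the infusion. Seated BP is also the only BP on Days 22, 43 and 85 and at ET.

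If the text is left alone, the baseline will be chosen during programming. Protocol 10.3.6 describes the sponsor team as unblinded for data review during the study, so the choice is better written down in advance.

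**Working it through.** No power or alpha figure is involved. The check is a count of scheduled readings against each baseline rule.

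**Inputs, from the Schedule of Activities**

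| Measure | Last scheduled reading before dosing | Day 1 predose reading? | BP readings after dosing starts |
|---|---|---|---|
| Seated BP | Day -1 | No | Day 1 at 5–15 min and 1 h; Days 22, 43, 85; ET |
| AOBPM | Day 1 predose | Yes | Day 1 at 6 h; Days 2–8 (Days 5–7 subcutaneous cohorts only), 15, 29, 57 |
| Seated pulse rate | Day 1, within 1 h before dosing | Yes | – |
| Body temperature | Day 1 predose | Yes | – |

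The Day 1 timing of seated BP comes from that row's own note, so it does not depend on how the table columns line up. The later days are read from column positions. The neighbouring rows show how the schedule marks a predose reading when one is meant.

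**Formula (SAP 9.1).** Change at time t = value at t − the subject's own baseline.

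**Scheduled post-dose seated BP timepoints.** 2 (Day 1) + 1 (Day 22) + 1 (Day 43) + 1 (Day 85) = 5, plus ET where it occurs.

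**SAP rule (Day 1 predose).** Scheduled seated BP readings that qualify: 0. Timepoints with a computable change: 0 of 5, and none at ET.

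**Protocol rule (last evaluable value before dosing), applied within method.** Qualifying reading: Day -1, or screening if Day -1 is missing. Timepoints with a computable change: 5 of 5, and ET.

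**What is not touched.** In SAP 9.5.4 the concentration relationship, the repeated-measures models and the analysis of maxima all use AOBPM, which has its predose value.

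**Comparison inside the SAP.** SAP 9.5.3 takes the laboratory baseline as the scheduled assessment immediately before dosing. Wording of that kind would also work for seated BP.

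**The case against.** The strongest reply is that a Day 1 predose BP does exist, from AOBPM. The two BP rows interlock: they share only Day 1, at different times, and otherwise alternate. They could be read as one BP schedule with the predose AOBPM value as common baseline. Both methods use the same seated posture after 5 minutes' rest. This reading is plausible, but the SAP does not state it. AOBPM is a mean of the last three of four readings, and the documents describe no such averaging for seated BP. If that baseline is intended, it too needs a sentence.

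A second reply is that the SAP need not be taken as abandoning the protocol rule. Section 3 promises to identify substantial differences and Section 11 identifies none, so Day 1 predose may be shorthand that happens to fit every vital sign except seated BP. The table shells, which are not in the documents, might settle it. That is a fair account of how the gap arose, but the governing text still fails when followed.

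A third reply concerns consequence, and it stands. Observed seated BP is summarised and listed whatever the baseline, no reading is lost, the study is not powered for hypothesis testing, and the one anticipated risk named in protocol 3.3 is a fall in heart rate, for which seated pulse rate has a predose reading.

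A reader might infer that borrowing the AOBPM value would create a false shift in BP. The documents give no size for any offset between methods, and an average offset would apply to active and placebo subjects alike, so it would largely cancel in comparisons with pooled placebo. It is a reason not to mix methods silently, not a demonstrated bias.

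**Conclusion.** The point holds for seated systolic and diastolic BP only. Under SAP 9.5.4 as written, descriptive change from baseline is undefined at all 5 scheduled post-dose timepoints and at ET; under the protocol's rule it is defined at all of them. The SAP departs from the protocol here, and Section 11 does not say so. It should be corrected, but it is a contained fault in descriptive summaries and figures.

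Two stronger readings are not supported:

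- A reader might conclude that the primary vital-sign endpoint cannot be assessed. The endpoint is clinically significant changes, and nothing in the documents makes that judgement depend on a computed seated BP difference.
- A reader might multiply timepoints, parameters and subjects into a total of lost values. The documents fix no such total. The safety population is everyone dosed, with up to 70 enrolled, rather than the 48 with sufficient evaluable data; attendance and the number of ET visits are unknown; and the readings themselves are still collected.

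The conclusion assumes that sites follow the schedule (an unscheduled predose seated reading could exist for some subjects) and that the table shells do not already define a separate seated BP baseline.

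**What to change.** In SAP 9.5.4, replace the baseline clause with the protocol 10.3.1.2 rule, taken within measurement method: the last evaluable reading before dosing by the same method. That is normally Day -1 for seated BP, and Day 1 predose for AOBPM, seated pulse rate and body temperature. The same-method condition is an addition to the protocol wording; without it, the predose AOBPM mean could be taken as the last BP value before dosing. List any remaining difference from the protocol in SAP Section 11.

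The cost is one sentence, with no new data, visits or procedures. The small downside is that the Day -1 reading is taken the day before dosing and is not matched for time of day, whereas protocol 9.4.2 ties AOBPM after Day 1 to roughly the predose time. A table footnote naming the baseline day would be enough to tell the reader.

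### SAP 9.5.4 asks for the same AOBPM dose-minus-placebo contrasts with and without baseline adjustment, and does not say which set is interpreted

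*Combined protocol and SAP*

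**What the plan says.** SAP 9.5.4 (Vital signs) plans, for the AOBPM data, that "a repeated-measures statistical analysis of absolute and change from baseline vital sign measurements will be produced". The fixed effects are treatment, timepoint and their interaction, together with "baseline as a covariate (for the change from baseline analysis"). The parenthesis confines the covariate to the change model. Earlier in the section baseline is fixed: "where baseline is defined as the Day 1 predose assessment".

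The sentences that follow name no outcome, so they apply to both models: "The primary contrasts of interest are each dose level versus placebo at each timepoint", and "Least squares means as well as a 90% CI of the mean difference between each dose level and placebo will be obtained". The covariance rule is also common to both: "An unstructured covariance structure will be used and a compound symmetric structure can be used if the model fails to converge". The example code covers only the change model: "model change = baseline treatment timepoint treatment*timepoint".

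The protocol does not settle the matter. Section 10.3.1.2 has a concentration model and a maximum-value comparison, the latter a "linear model with dose as a factor and baseline mean value of the corresponding analysis variable as a covariate". It does not describe this repeated-measures comparison with placebo. SAP Section 11 reports no changes from the protocol's analyses.

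**The concern.** Change from baseline is the absolute value minus baseline, so the two models address the same dose-minus-placebo question. They give different answers only because one omits the baseline covariate. Nothing in either document ranks them or calls one supportive.

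The omission is out of line with the rest of the SAP. The PD repeated-measures model (9.4.1) and the AOBPM maximum-value model (9.5.4) both adjust for baseline, and the second of these also has an absolute outcome. The absolute-value repeated-measures model is the only comparison with placebo that does not, and no reason is given.

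What is at stake is the estimate of a heart-rate fall. Protocol 3.3 names a decrease in heart rate as the only anticipated risk. The maximum-value analysis is not aimed at a fall, and SAP 9.5.5 says ECG data will not be presented. The repeated-measures pulse-rate contrasts are therefore the main modelled comparison with placebo for that risk. A reader given two intervals for one visit needs to know which to read.

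**Working it through.** **Inputs from the documents**
- Evaluable subjects: 48, as 36 active and 12 placebo (Protocol 5.2; SAP 7). The 3:1 ratio in Protocol 7.2 reproduces this: 48 × 3/4 = 36 and 48 × 1/4 = 12.
- Six dose cohorts with placebo pooled (SAP 5 and 6). With equal cohorts, which is an assumption, 36/6 = 6 active per dose against 12 placebo.
- CI level: 90% (SAP 9.5.4).

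**Assumptions, not in the documents:** SD 10 units at baseline and postdose; baseline-to-visit correlation ρ of 0.3 to 0.8; no missing data; one visit in place of the full repeated-measures model.

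**Step 1. The covariate is the source of the difference.** If change = a + b·baseline + treatment terms, then absolute value = a + (b + 1)·baseline + the same treatment terms. With baseline in both, the contrasts and residual variance are the same. A numerical check gave a maximum difference between estimates of 8e-14 and equal residual variances.

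**Step 2. Precision.**
- Without baseline: SE = SD·√(1/12 + 1/6) = 10 × 0.5 = 5.0.
- With baseline: SE ≈ 5.0·√(1 − ρ²).
- The ratio is 1/√(1 − ρ²): 1.09 at ρ = 0.4, 1.25 at 0.6 and 1.67 at 0.8. Simulation, which also pays for estimating the slope, puts the unadjusted SE 8%, 24% and 65% higher.
- To first order this ratio does not depend on the group sizes.

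**Step 3. Gap between the two estimates.** The gap is the baseline slope times the observed baseline difference. At ρ = 0.6 its SD is about 0.6 × 10 × 0.5 = 3.0 units.

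| ρ | Mean 90% CI half-width, absolute | Mean 90% CI half-width, adjusted | Median gap | 90th percentile of gap | Contrasts with no true effect where only one CI excludes zero |
|---|---|---|---|---|---|
| 0.3 | 8.35 | 8.07 | 0.8 | 2.7 | 4.9% |
| 0.6 | 8.33 | 6.76 | 1.9 | 5.0 | 10.1% |
| 0.8 | 8.36 | 5.08 | 2.7 | 6.6 | 13.5% |

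(4,000 simulated trials per ρ; 7 groups; t intervals on 41 and 40 df.)

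**Step 4. One worked visit, ρ = 0.6.** Suppose the active group starts 5 units above placebo and ends 5 below.
- Absolute model: −5 ± 1.683 × 5.0, so −13.4 to 3.4.
- Adjusted model: estimate −5 − 0.6 × 5 = −8.0. SE = 5 × 0.8 × √(1 + [25/(41 × 100)]/0.25) = 4.05. CI −8.0 ± 1.684 × 4.05, so −14.8 to −1.2.

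The same subjects at the same visit give one interval that includes zero and one that does not.

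**The case against.** **Nothing depends on these intervals.** The sample size is not based on a powered test (SAP 7). The primary endpoints in Table GZEA.1 are adverse events and clinically significant changes, not model contrasts. The interruption criteria in Protocol 7.4.1 are based on adverse events. This stands in full.

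**A reader might infer an inflated error rate.** Under no effect, the chance that at least one of the two intervals excludes zero is about 0.148 at ρ = 0.6 (0.131 to 0.169 for ρ of 0.4 to 0.8), against 0.10. The documents do not support that reading. No test is declared, and the figure describes only a reader who picks whichever interval suits. Each interval is valid on its own under randomisation. The volume of intervals also swamps it. The Schedule of Activities gives 8 postdose AOBPM timepoints for IV and 11 for SC cohorts, so (3 × 8 + 3 × 11) × 3 parameters = 171 contrasts per model, about 17 of which would exclude zero by chance.

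**A reader might tie the word primary in "The primary contrasts of interest are each dose level versus placebo at each timepoint" to the primary endpoint.** It only picks the comparisons of interest from all the pairwise differences that the code would print.

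**Reporting each contrast twice is not certain.** Only the change model is coded, and the displays are defined in a TFL shell document that is not available here. That is a fair limit. But the text says both analyses will be produced, and an example program is not a rule of precedence.

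**The absolute model has a use.** It gives LS means in mmHg and beats per minute. Also, the SAP does not say whether Day 1 predose is itself a response timepoint in that model. If it is, baseline cannot sensibly be a covariate as well, which might explain the parenthesis. This stands and limits the second option in the fix.

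**Group sizes may differ.** Appendix 6 of the protocol says Cohort 4 is to be repeated, and the safety population includes everyone dosed. Larger groups shrink the baseline imbalance but barely move the SE ratio.

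**Conclusion.** The point holds as one of precision and clarity. SAP 9.5.4 specifies an adjusted and an unadjusted version of the same AOBPM contrasts and does not say which is interpreted. The unadjusted version has an SE about 8% to 65% larger for an assumed ρ of 0.4 to 0.8. It also carries chance baseline imbalance between about 6 and 12 subjects, and can disagree with the adjusted version at the same visit.

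The sizes rest on an assumed correlation and, for the gaps and the worked visit, an assumed SD of 10. They also rest on equal cohorts and a single-visit model. That the two versions differ needs none of these assumptions, only a baseline slope in the absolute-value data that is not zero. The documents do not support reading this as a flaw in error control, in dose escalation or in the primary endpoint.

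**What to change.** In SAP 9.5.4, state that dose-minus-placebo estimates and 90% CIs for AOBPM come from the baseline-adjusted change model only, and that these are the contrasts interpreted. Present absolute values as descriptive summaries or LS means, without a second set of contrasts.

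Alternatively, if the absolute-value model uses postdose timepoints only, say so and add Day 1 predose AOBPM as a covariate. Its contrasts then coincide with those of the change model. This option does not suit a model in which Day 1 predose is a response timepoint.

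The first option costs one sentence, because the change model is already coded. The second costs a sentence and one model term. The predose reading is already in the Schedule of Activities, so neither needs new data, and LS means on the clinical scale are kept. The TFL shells should be checked to match.

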#### 3.3. Benefit/Risk Assessment

LY3475766 has not been administered to humans. The nonclinical safety information for LY3475766 supports the transition from preclinical status to clinical development. Based on the mechanism of action and nonclinical data, LY3475766 is not considered to be a high uncertainty compound. The only potential risk that is anticipated relates to the finding of a nondose-dependent decrease in heart rate in a 1-month Good Laboratory Practice toxicology study that was performed in cynomolgus monkeys; there were no adverse events (AEs) or any significant electrocardiogram (ECG) findings associated with the decrease in heart rate. Refer to the IB for LY3475766 for more details. This risk is considered to be monitorable and manageable at the planned doses of 10 mg, 30 mg, and 1000 mg IV and 100 mg, 300 mg, and 600 mg SC for LY3475766 in dyslipidemic but otherwise healthy subjects.

More information about the known and expected benefits, risks, serious adverse events (SAEs), and reasonably anticipated AEs of LY3475766 can be found in the IB.

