## **7.2. Method of Treatment Assignment**

Subjects who meet all criteria for enrollment will be randomized to 1 of the study treatment groups on Day 1. Subjects will be randomized in a 3:1 ratio to receive LY3475766 or placebo.

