## 7. SAMPLE SIZE JUSTIFICATION

Up to 70 subjects may be enrolled so that 48 subjects (LY3475766: 36, Placebo: 12) have sufficient evaluable data.

The sample size is customary for Phase 1 studies evaluating safety and PK, and is not powered on the basis of statistical hypothesis testing.

Subjects who are randomized and who are discontinued from the study (providing that discontinuation was not as a result of a safety finding) may be replaced to ensure that enough subjects complete the study.

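### The main AOBPM contrasts are 57 separate dose-by-timepoint differences per variable; adding time-averaged contrasts, per dose and pooled, would measure a heart-rate fall far more precisely

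*Combined protocol and SAP*

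**What the plan says.** SAP 9.5.4 fits a repeated-measures model to AOBPM systolic pressure, diastolic pressure and pulse rate, with treatment, timepoint and their interaction. It then states: "The primary contrasts of interest are each dose level versus placebo at each timepoint". On output it adds: "Least squares means as well as a 90% CI of the mean difference between each dose level and placebo will be obtained". The example code requests the differences with "lsmeans treatment*timepoint / cl pdiff alpha=0.1", with no multiplicity option and no estimate over doses or over time.

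The model is run on absolute values and on changes, with "baseline as a covariate (for the change from baseline analysis"). The absolute-value version therefore has no baseline term.

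Protocol 3.3 says: "The only potential risk that is anticipated relates to the finding of a nondose-dependent decrease in heart rate", a finding from a one-month monkey study. In the Schedule of Activities the AOBPM row has the note: "Days 5 through 7 are SC only. See Section 9.4.2. for more details". SAP 7 gives the size: "Up to 70 subjects may be enrolled so that 48 subjects (LY3475766: 36, Placebo: 12) have sufficient evaluable data".

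**The concern.** An effect that does not depend on dose is best sought by combining doses and days. The SAP instead gives the lead place to the finest split available, in groups of about 6. Each interval is wide, and there are so many that some will exclude zero by chance in most trials. The report would show scattered exclusions among many inclusions, with no single estimate of how far LY3475766 moves pulse rate against placebo.

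The other planned analyses do not supply that estimate:

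- The concentration slope in SAP 9.5.4 has no placebo term, and Protocol 9.5.1 plans no assay of placebo samples. An effect that is flat across doses can give a flat slope.
- The per-subject maximum over 3 and 9 weeks is poorly suited to showing a fall.
- Under SAP 9.5.5, ECG data will not be presented.

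**Working it through.** **Inputs from the documents.** The plan has 48 evaluable subjects, 36 active and 12 placebo, in six cohorts randomized 3:1 (SAP 7, Protocol 7.2). That gives 36/6 = 6 active and 12/6 = 2 placebo per cohort. Intervals are 90%, so the error rate is 5% per direction. There is no power, SD, correlation or effect size to reproduce.

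**Number of contrasts.** Post-dose AOBPM times for IV cohorts are Day 1 6 h and Days 2, 3, 4, 8, 15, 29 and 57, which is 8. SC cohorts add Days 5, 6 and 7, which makes 11. With three doses by each route, 3 × 8 + 3 × 11 = 57 per variable.
- 6 doses × 8 common times = 48 contrasts of about 6 vs 12.
- 3 SC doses × 3 days = 9 contrasts of about 6 vs 6, since only SC placebo subjects are measured on those days.

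**No effect.** The expected number excluding zero is 57 × 0.10 = 5.7, of which 57 × 0.05 ≈ 2.9 lie below zero. If all 57 were independent, the chance of at least one exclusion would be 1 − 0.9^57 = 99.8%. Simulating the actual layout with shared placebo (20,000 trials per setting, equal correlation between timepoints):

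| Within-subject correlation | At least one excludes 0 | At least one false fall |
|---|---|---|
| 0 | 99.4% | 89% |
| 0.3 | 98.5% | 78% |
| 0.5 | 96.3% | 68% |
| 0.7 | 90.6% | 58% |
| 0.9 | 75.4% | 43% |

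Under a subject-effect model with raw correlation r, the correlation left after baseline adjustment is r/(1 + r), at most 0.5. With between-subject/visit SDs of 8/5 bpm, r = 64/89 = 0.72, which leaves 0.42. Simulating that model directly gives about 97% and 72%.

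**A uniform 5 bpm fall (assumed).** Let b and w be the between-subject and visit SDs and T = b² + w². After baseline adjustment, the variance is:
- T − b⁴/T at one timepoint;
- b² + w²/8 − b⁴/T for the mean of the 8 common timepoints.

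The SE multiplies the SD by √(1/6 + 1/12) = 0.5 for one dose, or by √(1/36 + 1/12) = 1/3 for all doses pooled. At 8/5:
- Single contrast: 89 − 4096/89 = 42.98, SD 6.56, SE 3.28.
- Time-averaged: 64 + 3.125 − 46.02 = 21.10, SD 4.59, SE 2.30 per dose and 1.53 pooled.

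Power is the chance that the 90% interval lies wholly below zero (noncentral t, 48 − 8 = 40 df):

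| SDs b/w (bpm) | Single, 6 vs 12 | Per dose, time-averaged | All doses, time-averaged |
|---|---|---|---|
| 6/4 | 60% (SE 2.60) | 86% (SE 1.81) | 99% (SE 1.21) |
| 8/5 | 44% (SE 3.28) | 69% (SE 2.30) | 94% (SE 1.53) |
| 8/7 | 30% (SE 4.38) | 52% (SE 2.91) | 81% (SE 1.94) |

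Simulation agrees to within about three points. The 6 vs 6 contrasts are weaker: at 8/5, SE 6.56 × √(1/3) = 3.78 and power 36%. If the SD at one timepoint is instead taken directly as 5 to 12 bpm, a 6 vs 12 contrast misses the fall in 36–79% of trials.

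**Absolute-value model without baseline, at 8/5.** SE = √89 × 0.5 = 4.72, and power is about 27%.

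**Can the set separate effect from no effect?** At 8/5, the expected number of intervals below zero under the uniform fall is 48 × 0.44 + 9 × 0.36 ≈ 24 of 57, against 2.9 under no effect.

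**Cost of pooling, at 8/5.** Suppose only the top three doses lower pulse by 5 bpm.
- If the fall lasts through Day 29, the pooled mean is 5 × 3/6 × 7/8 = 2.2 bpm. With SE 1.53, power is about 42% (normal approximation, Φ(2.19/1.53 − 1.645)).
- If it lasts through Day 57, the mean is 2.5 bpm and power is about 48%.

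**Cohort 4 repeat (Appendix 6).** If a full cohort is repeated, the 300 mg contrasts become about 12 vs 14. At a single-timepoint SD of 6, power rises from 51% to 68%. The chance of at least one false exclusion stays at 96.3% for correlation 0.5.

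**The case against.** The strongest reply is that this is descriptive Phase 1 safety reporting. SAP 7 says the sample size is not powered for hypothesis testing. The primary endpoints are adverse events and clinically significant changes, and escalation does not depend on these intervals. The word primary may only pick the dose-versus-placebo differences out of all the pairwise differences the code prints. Unadjusted estimates by dose and time are ordinary in an ascending-dose study.

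Much of this stands. A reader might infer that the plan declares a false pulse signal in about 97% of null trials. It does not: the SAP has no rule that one interval excluding zero is a finding. The 97% also depends on an assumed correlation and counts rises as well as falls. A reader might also infer that the 57 contrasts cannot tell a real effect from none. The counts above, about 3 against about 24, show otherwise for a uniform fall.

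It is also fair to object to making the all-dose pool the only main contrast. The nondose-dependent finding comes from monkeys, and Protocol 5.5 puts the 10 mg dose at about half the estimated minimal-effect dose, so equal effects from 10 to 1000 mg are not assured. Pooled power falls by about half if only the top three doses act.

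What the reply does not meet is that the SAP itself ranks contrasts and chooses the least precise set from a model that can give better ones at no extra cost.

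**Conclusion.** The point holds as a problem of precision and readability. The count of 57 and the average of 5.7 chance exclusions per variable follow from the documents alone, given valid 90% intervals. The rest rests on assumptions: correlation 0 to 0.9 for the 75–99% (any exclusion) and 43–89% (false fall), and a uniform 5 bpm fall, SDs of 6/4 to 8/7 bpm and complete data for the power figures. Across those SDs, time-averaging raises detection from 30–60% for a single contrast to 52–86% per dose and 81–99% pooled. The pooled gain shrinks if only some doses act, so the per-dose and pooled estimates are needed together. The case for adjusting the absolute-value model is simpler: the baseline is already collected, and leaving it out only widens the intervals.

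**What to change.** In SAP 9.5.4:

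1. Add two sets of contrasts to the change-from-baseline model, with 90% intervals and pulse rate as the lead variable: (a) each dose minus placebo, and (b) all LY3475766 doses combined, weighted by number of subjects, minus placebo. Average each over the timepoints common to IV and SC cohorts (Day 1 6 h and Days 2, 3, 4, 8, 15, 29 and 57). Name (a) and (b) together as the main summary contrasts, and keep the dose-by-timepoint differences as supporting descriptive output. The 3:1 allocation within each cohort keeps route balanced in (b).
2. Add baseline as a covariate to the absolute-value model, in which case its contrasts equal those of the change model, or report no dose-versus-placebo contrasts from the unadjusted version.

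The cost is a few sentences and ESTIMATE statements in a model already planned, with no new data or visits. The downside is that averaging dilutes an effect confined to one day, and pooling dilutes one confined to some doses. The detailed differences stay in the tables for those cases. Because the sponsor team sees unblinded data during the study (Protocol 10.3.6), fixing the summary contrasts in advance also limits selective reading of the 57 intervals.
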